**Table 3 T3:** **Incentives used in the*****Legacy for Children***^***TM***^**study**

			**University of Miami**			**UCLA**		
**Group**	**Periodicity**	**Purpose**	**Staff**	**Location/mode**	**Incentive**	**Staff**	**Location/mode**	**Incentive**
Comparison	Every six weeks	Maintenance contact	Trackers	Phone call	-			
	Annually	Holiday gift	Trackers	mail	$20			
Intervention	Prenatal – 36 m Weekly blocks	Group meetings				Int staff	Site	Meal/Child care ($25)
	Prenatal – 36 m After blocks	Home visits				Int staff	Home/site	Gifts/Materials
	Prenatal – 36 m before blocks	Session schedule reminder				Int staff	Mail	-
	0-60 m Weekly	Group meetings	Intervention staff (Int staff)	Site	Diapers/toys Child care ($20), small gifts			
	0-60 m monthly	Group meetings	Int staff	Site	$5 per attended visit			
	0-60 m yearly	Personal follow- up visits	Int staff	Home/site	tape			
	Annually	Holiday gift	Int staff	Site	$20			
	Annually	Parent Satisfaction	Assessors	Phone	$50	RTI	Phone	$50
Intervention subsample	Periodically	Focus group	Assessors	Site	$50	RTI	Site	$50
	Annually	Case studies	Assessors	Site	$50	RTI	Site	$50
Intervention and Comparison	Annually/ December	Holiday gift	Int staff/Trackers	Mail	$ ≤ 20			
	Annually	Mother birthday greeting	Int staff/ Trackers	Mail	-	Int staff	Mail	-
	quarterly	For complete assessments				Int staff	Mail	$25
	6 m	Assessment	Assessors	Assess office	$100	Assessors	Assess office	$100
	9 m	FUI	Trackers	Phone/home	$10	Trackers	Phone/home	$10
	9 m	FUI						
	12 m	Birthday greeting	Int staff/ Trackers	Mail	-	Int staff	Mail	-
	12 m	Assessment	Assessors	Assess office	$100	Assessors	Assess office	$100
	12 m	Assessment Home	Assessors	Home	$50	Assessors	Home	$50
	15 m	FUI	Trackers	Phone/home	$10	Trackers	Phone/home	$10
	15 m	FUI						
Intervention and Comparison	21 m	FUI	Trackers	Phone/home	$10	Trackers	Phone/home	$10
	21 m	FUI						
	24 m	Birthday greeting	Int staff/Trackers	Mail	-	Int staff	Mail	-
	24 m	Assessment	Assessors	Assess office	$100	Assessors	Assess office	$100
	~ > 24 m	Finger stick	Phlebotomist	Home	$50	Phlebotomist	Home	$50
	27 m	FUI	Trackers	Phone/home	$10	Trackers	Phone/home	$10
	33 m	FUI	Trackers	Phone/home	$10	Trackers	Phone/home	$10
	33 m	FUI						$10
	36 m	Birthday greeting	Int staff/Trackers	Mail	-	Int staff	Mail	-
	36 m	Assessment	Assessors	Assess office	$100	Assessors	Assess office	$100
	39 m	FUI	Trackers	Phone/home	$10	Trackers	Phone/home	$10
	42 m	FUI	Trackers	Phone/home	$10	Trackers	Phone/home	$10
	45 m	FUI	Trackers	Phone/home	$10	Trackers	Phone/home	$10
	45 m	FUI						
	48 m	Birthday greeting	Int staff/Trackers	Mail	-	Int staff	Mail	-
	48 m	Assessment	Assessors	Assess office	$100	Assessors	Assess office	$100
	48 m	Assessment Home visit	Assessors	Home	$50	Assessors	Home	$50
	51 m	FUI	Trackers	Phone/home	$10	Trackers	Phone/home	$10
	54 m	FUI	Trackers	Phone/home	$10	Trackers	Phone/home	$10
	57 m	FUI	Trackers	Phone/home	$10			
	57 m	FUI				Trackers	Phone/home	$10
	60 m	Birthday greeting	Int staff/Trackers	Mail	-	Int staff	Mail	-
	60 m	Assessment	Assessors	Assess office	$100	Assessors	Assess office	$100
Intervention and Comparison subsample	Pregnancy	Fetal monitoring				Specialist	Site	$50
							

Another key factor to facilitate mothers’ participation in the assessment and intervention component was overcoming common barriers to attendance. Both sites provided van transportation to assessment and intervention activities to any mother who wanted it. To maximize mothers’ ability to attend group meetings, van scheduling accommodated parents to the extent that was possible. In Miami, the decision was made to conduct meetings during the week. Initially, pilot Miami groups were conducted during the day but, as mothers returned to full-time employment, evening groups were added. In LA, all group meetings were initially conducted on the weekends, but experience with the pilot study showed that some weekday groups were necessary.

When a family moved out of the catchment area, the sites attempted to maintain communication with the mother so that future assessments could still be conducted. Mothers who returned to the area were invited back to participate in intervention and/or assessments during the course of the study. Reasons for non-retention (i.e., nonparticipation in any of the assessments) were documented on an individual basis.

### Analytic sample size and statistical power

#### Retention and sample size

Table 4 reports the sample sizes for *Legacy* in terms of the number of completed assessments through age 5, with a full description of retention and participant loss by randomization group depicted in Figure 3. Although the *Legacy* impact assessment has been extended beyond age 5 and continues into school-age, the following discussion is constrained to the original impact assessment, conducted through age 5.

**Table 4 T4:** **Sample size for*****Legacy for Children***^***TM***^**, by site, year, and intervention status**

	**Los Angeles**			**Miami**		
**Year**	**Intervention**	**Comparison**	**% of Randomized Retained (n = 306)**	**Intervention**	**Comparison**	**% of Randomized Retained (n = 300)**
Baseline	165	120	93%	173	116	96%
1	138	100	78%	162	106	89%
2	136	92	75%	153	102	85%
3	127	79	67%	136	89	75%
4	124	78	66%	127	81	69%
5	117	73	62%	122	73	65%

**Figure 3 F3:**
[figure not shown]
**CONSORT Flowchart for the Legacy for Children**^**TM**^** project.**

The study began with a total of 338 intervention and 236 comparison baseline assessments, which represents 94% of the 361 mothers randomized to intervention and 96% of 245 mothers randomized to comparison. Baseline sample sizes were similar for the two sites. The mean assessment window for each assessment wave was within four to six weeks of the target date, from baseline to five years. Within each site, annual retention rates for each assessment wave were comparable across the two randomization groups. The sample sizes for each annual assessment are presented in Table 4 and culminate in Year 5 assessment rates of 64% across the two sites.

Attendance at group intervention sessions varied by site. In Miami, 90% of mothers attended at least one group session during the course of intervention provision. In LA, uptake was lower, with 78% of mothers attending at least one group session over the three years that intervention was delivered at the site.

### Measurement

In order to address the research questions of interest, three main categories of data were collected: a) process data on the intervention implementation and the mothers’ responses to the intervention; b) assessment data on mediating, moderating, and outcome variables; and c) cost data collected separately for intervention and research components. To develop and test the measurement protocol, complete data were collected for all participants in the pilot study, including process, outcome, and cost data.

#### Process measures

The process measures served several purposes. The first purpose was to determine the quality and fidelity of the intervention as implemented in each site for each of the key components included in the intervention design (e.g., parent groups, one-on-one visits, sense of community building efforts). In addition, the process measures provided feedback for formative purposes and ongoing assessment of program performance. This feedback was used to assist the intervention team in targeting training and technical assistance activities over the period of the study. Further, these data were used by the sites to monitor ongoing operations, in order to reduce their data burden and maintain investment in the study. Finally, the process measures contained qualitative information as a measure of intermediate outcomes (e.g., persistence of families in the program, engagement of participants) and key program components to assist in interpreting quantitative outcomes.

In short, the process measures were collected to evaluate whether the intervention conforms to the hypothesized model, whether the intervention was working and how it could be improved, the extent to which the intervention group actively participated in the program, and the causes and consequences of participant attrition. Thus, the process measures were used for both formative and summative evaluation.

#### Data sources

The process data consisted of time-based measures dependent on the mother’s random assignment to the intervention or comparison group. The process data were compiled from four data sources: (1) direct observation, (2) program record data, (3) data from program providers and (4) data from program participants.

##### Direct observation measures

A portion of all intervention sessions were directly observed by ethnographers. They followed selected groups at each of the sites throughout the *Legacy* project, but also observed other groups intermittently to document responses of different groups to similar intervention contents. The ethnographers described the *Legacy* meetings in detailed notes which were later coded and themed by trained and reliable coders.

##### Program record data

Program record data consisted of information about attendance and assessment rates, one-on-one visits, and information about contacts between *Legacy* staff and mothers. Forms were used to record information regarding one-on-one visits as well as individual contacts.

##### Data from program providers

Data were collected using interviews and questionnaires about how the group leaders perceived their success with the intervention as well as participants’ responses both on a group and individual level. At the completion of each group session, a parent group summary form was completed, documenting whether the session was completed as planned, as well as how mothers responded to the intervention and each other. A parent engagement form was completed every 10 weeks by the group leader for each mother. In addition to information regarding how many sessions each participant attended, the group leaders were asked for information regarding the perceived interest and participation of each mother in the main topics covered, the *Legacy* group, and their child. Also, the group leader rated the quality of the mother’s observed interaction with her child. These data are being used to calculate the dosage of the intervention received and to provide cross-validation of information provided by the mothers on the quantitative assessments.

##### Data from program participants

These data were collected through interviews, questionnaires, and focus groups. Focus groups of 10–12 randomly chosen participants were conducted annually by an evaluator from the PCC to explore the mothers’ perceptions and responses to the intervention curriculum, group leaders, and other participants. For each site, five mothers were selected for in-depth case studies and participated in annual interviews by an evaluator. The focus groups and case studies served to generate narratives about overall project experiences and gave respondents a chance to tell their story.

In addition, parent satisfaction surveys were conducted systematically for a subsample of participants, selecting those who actively participated (i.e., attended at least one session in the 6 months prior to the annual assessment time point). This interview solicited information about the mothers’ satisfaction with *Legacy*, the group leader, and the activities they may have taken part in. In addition, the interview solicited information regarding parental self-efficacy and relationships with other parents in the group.

The data gathered from the pilot study on process measures were used to refine the instruments in an iterative process. For example, when mothers in focus groups as well as in some of the group sessions discussed that they felt that being in *Legacy* was a unique experience, unlike any other group setting, a question was added to the satisfaction survey to learn whether this perception was shared by the majority of mothers or not.

#### Demographic, mediating, and outcome measures

The quantitative assessments were selected to measure the three constructs of interest: child development, parent/family characteristics, and parental sense of community. These constructs will be used to determine the degree to which the *Legacy* intervention influences child development and to analyze the paths of those impacts. The outcome domains for child development include cognitive development, language development, socio-emotional functioning, behavioral functioning, and health. In addition, data were collected on other parent and family domains that were expected to be important as either control variables or as mediators. These consisted of demographics and family background, self-efficacy, parental responsibility, parental investment, devotion of time and energy, parenting behavior (including guidance of behavioral and emotional regulation and facilitation of cognitive development), and quality of the mother-child relationship. The parental sense of community domains included support/resources/memberships, community/peer relations, satisfaction of needs (life and self), and psychological sense of community.

#### Data sources

Assessments were administered at baseline, when the child reached 6 and 12 months, and then annually until the child reached 5 years of age. The baseline assessment was designed to measure maternal characteristics, attitudes, and knowledge before the beginning of the *Legacy* intervention. The intervention began prenatally in LA and postnatally in Miami; thus, the baseline was administered prenatally (before intervention attendance was permitted) in LA and when the infants were 4–8 weeks old in Miami.

These assessments were conducted by assessment staff from the PCC who were blind to the intervention assignment. As an additional precaution, assessments took place in a lab that was in a separate building from the intervention, and contact between assessment and intervention staff was limited.

The assessment batteries consisted of questionnaires, direct assessments, and some videotaped observations of mother and child. Most of the measures were standardized and had been previously used in similar research projects, but some questionnaires were developed or adapted for *Legacy*. The majority of the measures were administered in person using a computer assisted personal interviewing procedure; however, some sensitive questions, e.g., regarding alcohol and drug use were completed by the mothers alone, using an audio-enhanced computer-assisted self-completed interviewing process. For a complete list of measures by time point, see Table 5.

**Table 5 T5:** **Domain, constructs and measures by assessment time point in the*****Legacy for Children***^***TM***^**Study**

**Domain**	**Construct**	**Measures**	**B**	**6**	**12**	**24**	**36**	**48**	**60**
Maternal Constructs									
Mediating Variables									
*Self Efficacy*			X	X	X	X	X	X	X
	*Parental Self Efficacy*		X	X	X		X		X
		*Components of Maternal Efficacy*[63,64]	X	X	X		X		X
		*Competence Subscale of PSI*[65]	X	X	X		X		X
		*Self-Efficacy Scale*[66]	X	X	X		X		X
	*Knowledge and Expectations*		X	X	X	X		X	X
		*Future Expectations *[67]		X				X	X
		*Knowledge of Infant Development Inventory*[68]	X		X	X			
*Commitment, Satisfaction*				X	X	X	X	X	X
	*Commitment/Involvement*			X	X	X	X	X	X
		*Parental Commitment Scale*[69]		X	X	X	X	X	X
	*Parental Role Satisfaction*				X		X		X
		*Parenting Satisfaction Scale*[70]			X		X		X
*Emotional Well-Being*			X	X	X	X	X	X	X
	*Stress, Mental Health*		X	X	X	X	X	X	X
		*Parenting Stress Index-Life Stress*[65]	X		X		X		X
		*Parenting Stress Index-Short Form*[65]			X		X		X
		*General Life Satisfaction*[71]	X	X	X	X	X		X
		*SF Mental Health Index*[72]	X		X		X		X
		*CIDI Depression*[73]	X		X	X	X	X	X
	*Coping Skills*		X	X		X	X		X
		*Coping Resources Interview*[74]	X	X		X	X		X
*Sense of Community, Support, Connectedness*			X	X	X	X	X	X	X
	*Social Networks*		X	X		X	X		X
		*Duke-UNC Functional Social Support Questionnaire*[75]	X	X		X	X		X

In addition to the baseline and follow-up assessments, a family update interview (FUI) was administered by the tracking staff every six months of child age from 9 through 57 months. These interviews included questions concerning contact information, household composition, child care, and employment and services received and were conducted by telephone or in person.

##### Development of the assessment plan

The approach to selecting child and family measures was based on relevance to the intervention goals and specific research question. The assessments included all child outcome domains, maternal mediating domains, as well as demographics and family background variables. Whenever possible, measures for which standardization samples and norms matching the current sample were available, as well as documented reliability and validity with an internal consistency reliability (alpha coefficient) of at least .70, were selected. Whenever feasible, measures that were appropriate to the mothers’ expected reading and comprehension levels and their cultural backgrounds were selected.

Developmental change is rapid from birth to 5 years, the age ranged covered in the *Legacy* study. Therefore, many measures of child outcome focused on a relatively narrow age range. Thus, to measure a particular outcome at different ages, different outcome measures had to be selected for some domains (e.g., Brief Infant-Toddler Social & Emotional Assessment [65] for younger ages and Devereux Early Childhood Assessment [66] for older ages to assess social/emotional development). Additionally, to accommodate the possibility that some children might have developmental lags, particular attention was paid to the floor (and ceilings) of the selected measures. A major issue of concern was the burden of assessment on the participants. Where possible we chose shorter assessments, and selected the most feasible measures in terms of time and materials.

Even with these selection criteria, several measures that were tested with the pilot participant group were dropped or replaced for the main study. One major cause for changes in methods was the fact that while mothers were asked whether they planned to teach English to their child, in reality many mothers who were bilingual had children who were either bilingual or mono-lingual non-English speaking, particularly at the earlier ages (primarily Spanish). Therefore, measures were selected, that were suitable for bilingual children, and, when possible, allowed for administration in Spanish. Specifically, the Kaufmann Assessment Battery for Children [67] was selected to measure cognitive development because it can be administered bilingually. The Spanish version of the Preschool Language Scales [68] was also included for those children deemed dominant in Spanish (as attained by maternal interview on child’s language exposure and preference).

Other measures turned out to be too challenging for the participant group. For example, the child version of the Violence Exposure measure [69] was too complicated for many children and was dropped. The direct child assessments of cognition and language were alternated with language assessed at 2 and 4 years of age and cognition at 3 and 5 years of age and the Bracken Basic Concept [70] scale was dropped because the testing time was too long for the children.

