### Target population

#### Inclusion criteria

The cross-site inclusion criteria had several components -- one that defined the target population and two that were logistically necessary. Pilot data were used to examine recruitment procedures and feasibility of recruitment criteria. The first criterion was environmental risk for poor developmental child outcomes, which was operationalized differently by the two sites. Families were selected based on environmental risk rather than medical or biological risk. Therefore, both intervention sites recruited from well-care settings and excluded mothers reporting mental health or substance abuse problems.

The second two criteria were factors that were required to facilitate intervention provision. The first of these logistical necessities was comfort speaking and understanding conversational English, given that the intervention was conducted in English, the assessment instruments were largely available only in English, and it was not feasible at either site to create groups that could be conducted in other languages. A second such criterion related to custody and age; because the intervention included attendance by mothers and their children, only mothers who had custody of their children and who were of age to consent to their own participation (18) were included in the study. Mothers who lost custody during the course of the intervention were no longer eligible to participate.

In addition to the aforementioned cross-site *Legacy* inclusion criteria, each site elected to impose additional site-specific criteria. The original eligibility criteria for the UCLA project further restricted eligibility to women who lived within 10 miles of UCLA, planned to stay in the LA area for 3 years, and received their prenatal and well-baby medical care from the UCLA Medi-Cal Health Maintenance Organization (which is a public health insurance program which provides needed health care services for low-income individuals). For feasibility issues related to intervention and assessment provision, mothers who had more than 2 children (including the target child), or were expecting a multiple birth, if known at the time of recruitment (26 weeks), were not eligible.

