### Participant characteristics

The final participant characteristics for the 574 mothers who completed the baseline assessment appear in Table 1. Statistical comparisons of each sociodemographic characteristic across the two sites were conducted in order to identify site differences. *T*-tests were used to contrast the continuous sociodemographic items (e.g., maternal age) and Chi-square statistics were used to compare distributions across categorical demographic variables. The sites differed significantly on a number of maternal characteristics, including age, education, marital status, cohabitation, race/ethnicity, and employment. The participant groups were similar for factors that reflected the recruitment criteria, including household income and the proportion of mothers speaking English in the home. The two groups were also similar in the proportion of male children, mothers living in public housing, and for indicators of the mother’s household composition.

**Table 1 T1:** Baseline socio-demographics for mothers in the Miami and LA samples and the combined sample, by randomization group

	**Both sites (n = 574)**	**Miami (n = 289)**	**UCLA (n = 285)**	**Test of Difference***
	**%**	**%**	**%**	**p-value**
Maternal Age < 23	49.3%	57.1%	41.4%	.0002
Child Female	49.9%	53.2%	46.8%	.7718
Maternal Education				
Less than HS diploma	23.9%	27.7%	20.0%	<.0001
HS diploma/GED	59.4%	61.9%	56.8%	
Voc. Tech/Associate's Degree	12.4%	9.0%	15.8%	
College degree or more	4.4%	1.4%	7.4%	
Maternal Marital Status				
Married	22.1%	16.6%	27.7%	0.0191
Separated	4.9%	4.8%	4.9%	
Divorced	2.1%	1.7%	2.5%	
Widowed	0.5%	0.4%	0.7%	
Never Married	70.4%	76.5%	64.2%	
Live with a Husband/Partner	40.2%	33.2%	47.4%	0.0005
Race/Ethnicity (multiple selections allowed)				
Non-Hispanic Black	57.1%	69.2%	44.9%	<.0001
Non-Hispanic White	3.8%	1.0%	6.7%	0.0005
Hispanic	24.9%	9.0%	41.1%	<.0001
Haitian	8.5%	17.0%	0.0%	<.0001
Other	5.8%	3.9%	7.9%	0.0446
Employment				
Working full-time	10.3%	11.8%	8.8%	0.0004
Working part-time	15.5%	9.7%	21.4%	
Not working	74.2%	78.6%	69.8%	
Household Income				
<$20,000	50.2%	52.6%	47.7%	0.5726
$20,000-29,999	19.5%	17.3%	21.8%	
$30,000-39,999	10.5%	9.7%	11.2%	
$40,000-49,000	6.6%	6.9%	6.3%	
$50,000+	4.9%	4.2%	5.6%	
Missing (imputed for analysis)	8.4%	9.3%	7.4%	
Primary Language Spoken at Home				
English	98.3%	98.3%	98.3%	0.9823
Non-English Language	42.3%	34.6%	50.2%	0.0001
Spanish	28.4%	13.5%	43.5%	<.0001
Creole	10.8%	20.8%	0.7%	<.0001

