Other	5.8%	3.9%	7.9%	0.0446
English Spoken Most in Home	79.8%	85.1%	74.4%	0.0014
Home Ownership				
Owned	22.5%	29.2%	15.7%	<.0001
Rented	75.9%	69.8%	82.2%	
Occupied without rent payment	1.6%	1.0%	2.1%	
Lives in public housing	12.6%	14.5%	10.7%	0.1778
Household Composition		Mean		p-value
Number of adults living in home^	1.5	1.6	1.5	0.5781
Number of children living in home+	1.5	1.5	1.4	0.7054

* As indicated by Chi-square or *t*-test statistic, as appropriate.

^Excluding *Legacy* mother, top-coded at 6.

+ Excluding *Legacy* child.

Statistical comparisons of intervention and comparison groups were conducted within sites to identify any group differences that may have remained after group randomization. As depicted in Table 2, randomization of eligible participants to each of the two randomization groups within each site resulted in equivalence of groups across each measured sociodemographic characteristic.

**Table 2 T2:** Baseline socio-demographics for mothers in the Miami and LA samples and the combined sample, by randomization group

	**Miami (n=289)**		**LA (n=285)**	
	**%**		**%**	
	**Interv.**	**Comp.**	**Interv.**	**Comp.**
Maternal Age < 23	55.5%	59.5%	40.6%	42.5%
Child Gender				
Male	47.4%	49.1%	56.5%	46.1%
Female	52.6%	50.9%	43.5%	53.9%
Education				
Less than HS diploma	29.5%	25.0%	21.8%	17.5%
HS diploma or more	70.5%	75.0%	78.2%	82.5%
Marital Status				
Married	14.5%	16.4%	26.7%	27.5%
Not Currently Married	85.6%	83.6%	73.3%	72.5%
Live with a Husband/Partner	33.7%	31.0%	47.8%	45.3%
Race/Ethnicity (multiple selections allowed)				
Non-Hispanic Black	65.9%	74.1%	43.6%	46.7%
Non-Hispanic White	1.7%	0.0%	5.5%	8.3%
Hispanic	9.8%	7.7%	43.6%	37.5%
Haitian	18.5%	14.7%	1.2%	3.3%
Other	4.1%	3.5%	6.4%	4.6%
Employment				
Working full- or part-time	21.4%	21.6%	28.5%	32.5%
Not working	78.6%	78.5%	71.5%	67.5%
Household Income				
<$20,000	53.8%	50.9%	49.7%	45.0%
>= $20,000	38.7%	37.1%	42.2%	48.3%
Missing	7.5%	12.1%	7.9%	6.7%
Languages Spoken at Home				
Non-English language	34.7%	34.5%	50.9%	49.2%
	Mean		Mean	
Household Composition				
Number of adults living in home*	2.6	2.6	2.5	2.5
Number of children living in home^	1.4	1.5	1.4	1.5

* Excluding *Legacy* mother, top-coded at 6

^ Excluding *Legacy* child

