#### Analyses of outcome and mediating factors

In general, all intervention effects will be investigated using site- and time-point-stratified models first, using an ITT approach. Due to important implementation differences, site pooled models with site interaction included, will be considered carefully and used sparingly. The primary outcomes will be first examined using *t*-test and Chi-Square analyses to investigate individual outcomes as a function of *Legacy* group assignment. Multivariate statistical modeling will be used to address changes over time as well as the effects of mediating and moderating variables. Given the longitudinal nature of the data, trend analyses will be employed to test for linear and curvilinear relationships in the repeated measures over time. In the anticipated event that significant group differences are detected in maternal and child mediators and outcomes, multivariate linear and logistic regression techniques will be employed as a means of identifying effect modification and controlling for significant confounders. All regression modeling procedures will follow the general conceptual path of influence described in the *Legacy* Logic Model (Figure 2). Multiple ANOVA or regression models that account for correlation of outcomes within subjects will be employed to model the collective influence of intervention randomization on multiple measures of a single outcome domain (e.g., cognitive/language outcomes). In anticipation of an increasing amount of missing data over time, multiple imputation and nonresponse weighting will be used as alternative means of conducting ITT analyses within a general PROC MIXED regression framework.

A strength of the *Legacy* evaluation is a design in which many mediators and outcome variables are measured at multiple time points. This will allow a mixed model approach. In the first stage, growth curves are fit for individuals. Depending on the number of measurement, these curves may be linear, quadratic, etc. In the second stage, predictors such as intervention or comparison group assignment, demographic characteristics, and other predictors will be added and evaluated for their ability to predict slope and intercept parameters.

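### The age-2 and age-4 language comparisons rest on a test form chosen after randomisation from the mother's report, with Spanish the only alternative named; adjust them for baseline home language and tabulate form by arm

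*Protocol article*

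**What the plan says.** Under *Development of the assessment plan*, the article reports that many bilingual mothers had children who were bilingual or spoke no English, and that instruments were changed for this reason. For language: "The Spanish version of the Preschool Language Scales [68] was also included for those children deemed dominant in Spanish". Dominance is determined "as attained by maternal interview on child’s language exposure and preference". The same section places direct language testing at ages 2 and 4 and direct cognitive testing at ages 3 and 5. It says the cognitive test was selected because it can be given bilingually.

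Table 1 gives home languages in the order both sites, Miami, LA: "Creole 10.8% 20.8% 0.7" and "Spanish 28.4% 13.5% 43.5". It also gives "English Spoken Most in Home 79.8% 85.1% 74.4". Table 2 gives non-English home language by arm (Miami intervention, Miami comparison, LA intervention, LA comparison): "Non-English language 34.7% 34.5% 50.9% 49.2".

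*Inclusion criteria* states that "the intervention was conducted in English". Goal G5 is to help mothers further their children's verbal and cognitive development. *Recruitment and randomization* says that mothers were told their assignment.

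*Analyses of outcome and mediating factors* begins with t-tests and chi-square tests, by site and time point, "to investigate individual outcomes as a function of *Legacy* group assignment". Regression to control for confounders follows if significant group differences are found.

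**The concern.** Two features of the language outcome deserve attention.

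**Form choice comes after randomisation.** The form a child takes depends on what the mother says about exposure and preference at about age 2 or 4. She knows her arm. The programme is in English, includes the child in some sessions and aims at verbal development. It could therefore change either the child's dominant language or the mother's account of it. If the share of children taking the Spanish form differs between arms, and the two forms do not score alike, part of any language difference would come from the form. Blinded assessors do not prevent this, because the mother's report selects the form. The exposure is largest in LA, where 43.5% of homes speak Spanish.

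**The named alternative covers Miami's less common second language.** If some Miami children are Creole-dominant, the article does not say how they are tested or scored. Since sites are analysed separately first, any effect falls on the Miami language result alone.

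The first-line test uses no baseline language covariate, so nothing in that step absorbs language-related variation or shows a shift in form.

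**Working it through.** **1. The plan's own figures.**
- Power, from *Sample size and power*: effect 0.50 SD, 120 children per site, one-sided alpha 0.05. The normal approximation with 60 per arm gives 0.863, which agrees with the stated 0.86. At 72:48 (the 3:2 allocation) it gives 0.850. This figure is for the cognitive measure; none is stated for language.
- Table 1 pooled percentages, from site counts: Spanish (39 + 124)/574 = 28.4%; Creole (60 + 2)/574 = 10.8%; English spoken most (246 + 212)/574 = 79.8%. All three match.

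**2. How many children could be concerned.**
- Miami, Creole at home: 20.8% of 289 ≈ 60. Spanish at home: 13.5% of 289 ≈ 39. Ratio 60/39 ≈ 1.5.
- English not spoken most: Miami 100 − 85.1 = 14.9%, about 43 of 289; LA 100 − 74.4 = 25.6%, about 73 of 285.
- Creole-dominant children in Miami: not reported. With home language as a guide, between 0 and 14.9%. If the 14.9% split in proportion to the listed languages (Creole 20.8, Spanish 13.5, other 3.9), the share would be 14.9 × 20.8/38.2 ≈ 8.1%. That split is an assumption.
- In LA, Creole is 0.7%. The Creole question therefore concerns Miami, and the use of two forms concerns mainly LA.

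**3. Dilution (illustration).** Assume a share f of Miami children is tested in a language they do not command and shows no effect. Assume also that the true language effect is 0.50 SD, borrowed from the cognitive calculation. The expected difference is then 0.50 × (1 − f). The last column takes the Miami year-4 sample in Table 4 (127 and 81) and assumes all of them have a language score.

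| f | Diluted effect (SD) | Power, 60 + 60 | Power, 127 + 81 |
|---|---|---|---|
| 0 | 0.500 | 0.863 | 0.969 |
| 5% | 0.475 | 0.831 | 0.955 |
| 10% | 0.450 | 0.794 | 0.936 |
| 14.9% | 0.425 | 0.754 | 0.911 |

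**4. Bias from form choice (illustration).** Bias in SD = (difference between arms in the share taking the Spanish form) × (offset between forms in SD). The article gives neither input. Assuming 2 to 10 percentage points and 0.25 to 0.50 SD:
- lowest: 0.02 × 0.25 = 0.005 SD;
- highest: 0.10 × 0.50 = 0.05 SD.

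The highest value is a tenth of the 0.50 SD design effect. It is a fifth of 0.25, the upper limit the article cites for earlier parenting programmes.

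**5. Baseline balance.** Non-English home language is 34.7% against 34.5% in Miami and 50.9% against 49.2% in LA. The arms start level, so a form difference between arms would have to develop later. The balance also makes baseline home language a safe covariate.

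**The case against.** A reader might infer that Creole-dominant children are given the English form, that English and Spanish scores are pooled, and that the comparison therefore includes children it cannot measure. The article supports none of these.

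- It does not say what a Creole-dominant child takes, or how scores from the two forms are combined. An article may leave both to the full protocol or analysis plan. The copy of Table 5 at hand shows only maternal measures, so it cannot settle which child forms existed.
- No Creole-dominant child is documented. Creole at home is not Creole dominance: 98.3% of Miami homes list English, leaving about 1.7% (some 5 of 289) that do not. English is spoken most in 85.1%, mothers had to be comfortable in English, and the article describes the non-English-speaking children as mainly Spanish-speaking.
- The programme's direct English exposure of the child in LA is modest. One-hour sessions alternate between mother-child and mother-only, in 10-week blocks with breaks of 4 to 6 weeks. That is about 5 mother-child hours per 14 to 16 weeks, or roughly 20 minutes a week at full attendance. In LA, 22% of mothers (100 − 78) attended no group session.
- Testing a child in the dominant language is a defensible choice.

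All of this stands, and it rules out the stronger reading. It does not remove the two facts that remain: form choice follows randomisation and rests on an unblinded report, and the first-line comparison takes no account of baseline language. The later growth-curve stage allows demographic predictors, but the article does not name home language among them.

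**Conclusion.** The point holds as a low-cost improvement to the language analysis. It does not show that the language result is invalid. The form is selected after randomisation by a mother who knows her arm, and the only non-English form named is Spanish, although Creole is spoken in more Miami homes.

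Creole-dominant children, if there are any, would mainly weaken the Miami language effect and add noise. Their share is unknown, from zero to roughly 15% with home language as a guide. Bias needs form use to differ by arm; 0.005 to 0.05 SD is the range under the assumed inputs, not an estimate from the trial. The absence of a stated Creole rule is not by itself an error in an article.

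The cognitive measure, described as suitable for bilingual administration, and the power of 0.86 are untouched.

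**What to change.** 1. Keep all randomised children with a language score in the headline intention-to-treat estimate. Limiting the headline to English- and Spanish-speaking homes would conflict with the plan's own approach.
2. Prespecify, within each site, adjustment or stratification of the age-2 and age-4 language comparisons for baseline home language: English spoken most in the home (yes/no), plus Spanish or Creole spoken at home. Table 1 shows these were collected. Do not adjust for or stratify by the form taken at the visit, since that follows randomisation.
3. Tabulate form used by arm and site. Do not let the decision to combine the forms depend on what this table shows.
4. As a sensitivity analysis, give the estimate without homes where English is not spoken most and the other language is not Spanish. In Miami this removes at most about 43 of the 289 baseline families.

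The cost is one table and a covariate-adjusted model, from data already held. The gain in precision depends on how strongly home language predicts the score, which the article does not give. Adjustment does not fully remove a shift in form within a language stratum, so the table is needed to interpret the result.
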